## Introduction

### Effects of Therapy Monitoring and Feedback

For many years, monitoring and feedback procedures have been implemented in mental health care and in psychotherapy. Some researchers and practitioners identify these procedures as part of “good practice” [1] and even as the “most significant innovation in therapy practice within the past 20 years” [2]. Studies (case studies, implementation reports, and randomized controlled trials [RCTs]) tried to investigate the effects of monitoring and feedback in different mental health settings, applied to the treatment of many different diagnoses. Meta-analyses report small to medium overall effect sizes and showed that the feedback significantly reduces the odds of treatment dropout [3,4]. With respect to the effects, it has to be noted that the methodological quality of the studies is different and often poor [5], for example, pragmatic trials were realized with outcome assessments which were not independent of the process measures [6], and studies often are statistically underpowered (small, expected effect sizes require larger sample sizes) [7]. Other criteria concern the proof of using the feedback as intended—such as the manipulation check in an experiment—which, in case of not being taken for granted, may reduce the effect size of interventions compared to treatment as usual [8], and the implemented spectrum of outcome and progress measures [9].

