After the waiting period, a randomization procedure decides on the allocation of a patient to condition A (ASH) or B (ASH+synergetic process management [SPM]). To ensure methodological rigor and internal validity, patients will be randomly assigned to one of the two treatment conditions using therapist-specific block randomization. The predefined block-randomized allocation sequences (eg, ABAB, BABA, AABB, BBAA, ABBA, and BAAB) will be generated in advance by the principal investigator for each therapist to ensure a balanced distribution of conditions within therapists. Patients will be assigned to intervention conditions in the order of study inclusion according to the next position in the respective therapist’s allocation sequence. The allocation sequence will remain concealed from the therapists until each new patient is assigned.

After the randomization, the treatment period starts, whose length depends on the concrete requirements of each patient and must be decided by the patient and therapist together (shared decision-making). In contrast to manualized treatments (adherence to protocol), this is a usual procedure in naturalistic settings. A follow-up assessment will be conducted 6 months after the end of therapy.

There are four assessment points: at the beginning of the waiting period (T1), at the start of the treatment (T2), at the end of the treatment (T3), and at follow-up (T4). The design of this study is illustrated in Figure 1.

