### Power Considerations

The estimation of the sample size by power analysis refers to two research questions: (1) Is there a difference between the waiting period and the treatment? (2) Is there a difference between the two conditions of the treatment? The statistical procedure for answering these questions is ANOVA with repeated measures, with the groups (conditions) as the between-subject factor and the comparison of the waiting period (T1-T2, level 1) with the overall treatment (T2-T3, level 2) as the within-subject factor. The power calculation for estimating the sample size was realized by the software package G*Power (Heinrich-Heine-Universität Düsseldorf) [57].

The power estimation of the within-subjects calculation (waiting period versus overall treatment, independent of the condition) was based on the reported average effect size of psychotherapy outcomes from studies included in the meta-analysis (Cohen *d*=0.68) [58]. Using an effect size converter, this d value was transformed into Cohen f (f=0.34), which is needed for calculations in G*Power. The power was defined at 0.95, and the correlation between the measurement points was left at a default value of *r*=0.50. Sphericity was assumed. For two measurement points within the sample, it was estimated that the null hypothesis of no difference (no change) could be rejected with a probability of 96% if a sample size of 32 patients is included.

For the power calculation on the effects of the conditions (between-group comparison), a lower threshold value of the mean effect size was supposed at f=0.25, because of the lack of data in this case. The power was defined at 0.80. All other values and assumptions were the same for the between-subject factor as for the intersubject factor. It was estimated that the null hypothesis of no difference (no change) could be rejected with a probability of 80% if a sample size of 98 patients (49 in each condition) were included.

Based on the estimated sample sizes of 32 patients (hypothesis 1) and 98 patients (hypothesis 2), we defined the overall sample size of this study as 100 patients (n=50 in condition A: ASH; n=50 in condition B: ASH+SPM). The allocation ratio is 1:1 with 50 patients per arm.

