### Statistical Analysis

The statistical procedure for answering the outcome-related questions of this study is ANOVA with repeated measures, with the groups (conditions) as the between-subject factor and the comparison of the waiting period (T1-T2, level 1) with the overall treatment (T2-T3, level 2) as the within-subject factor. The preference ratings of the therapists in the ASH+SPM condition can be used as covariates in a 1-factor ANOVA with repeated measures.

The therapy effects can be predicted by linear regression models and multilevel regression models with conditions, therapy motivation (patients), alliance rates (patients), and the quality of the implementation as predictors. In the ASH+SPM condition, the preference of implementing the SPM (therapists) and the compliance rates (patients) of the process monitoring can also be used as predictors.

The research questions on the dynamics of change (eg, Are pattern transitions related to the outcome?) will be analyzed by applying the Pattern Transition Detection Algorithm [59] and methods of recurrence quantification analysis [60,61]. The respective quantifiers will be correlated with the outcome measures (T2-T3 and T2-T4).

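### The 80% power for ASH versus ASH+SPM belongs to an ANOVA term that averages in the pre-randomisation waiting period, so it is not the power to detect that effect during treatment

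*Protocol article*

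**What the plan says.** Power Considerations names two questions: waiting period against treatment, and ASH against ASH+SPM. It assigns both to one repeated-measures ANOVA. Statistical Analysis repeats the model, "with the groups (conditions) as the between-subject factor and the comparison of the waiting period (T1-T2, level 1) with the overall treatment". Treatment, from T2 to T3, is thus the second level.

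For the between-condition question, "a lower threshold value of the mean effect size was supposed at f=0.25, because of the lack of data in this case". On power: "The power was defined at 0.80". The remaining settings carry over from the within-subject calculation, where "the correlation between the measurement points was left at a default value of *r*=0.50" and two measurement points were used. The result is that the null hypothesis "could be rejected with a probability of 80% if a sample size of 98 patients (49 in each condition) were included", rounded up to 50 per arm.

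Study Design fixes when the arms come into being: "After the waiting period, a randomization procedure decides on the allocation of a patient to condition A (ASH"; the alternative is the feedback arm. T1 is the start of the waiting period, T2 the start of treatment and T3 its end. The same section says that baseline symptom severity, medication and concurrent treatment will be considered as covariates in the main outcome analyses. Power Considerations and Statistical Analysis do not carry symptom severity into the model.

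**The concern.** A between-subject main effect compares the arms on the average of the two levels. Here one level is the T1-T2 change, which is complete before anyone is allocated. Randomisation makes the expected arm difference in that level zero, so the main effect carries only half of any difference that arises during treatment. The power calculation nevertheless places the full f=0.25 (d=0.5) in the averaged effect.

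The carried-over correlation raises a second question. The default describes scores at measurement points, but the levels of this ANOVA are period changes. T2 enters those two changes with opposite signs, which pushes their correlation below zero.

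ASH against ASH+SPM is the only randomised comparison, and it alone drives the sample size; the other question needs 32 patients. If its real power is well below 80%, a null result could be misread as evidence that feedback adds nothing.

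**Working it through.** **Inputs.** f=0.25, N=98 (49 per arm), m=2 levels, r=+0.50 and power 0.80 come from Power Considerations. The definition of the levels comes from Statistical Analysis and the timing of randomisation from Study Design. Alpha is not stated; 0.05 is assumed because it reproduces the plan's results. For two equal groups d = 2f = 0.5.

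**Step 1: reproduce the stated figure.** For G*Power's between-factors test, the noncentrality is λ = f²·N·m/(1+(m−1)r) = 0.0625·98·2/1.5 = 8.17, with 1 and 96 df.
- Power is 80.8% at N=98 and 79.9% at N=96, so 98 is the smallest even N that reaches 80%.
- The within-between interaction option uses λ = f²·N·m/(1−r) and would need only N=34. The main effect was therefore the term powered.

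**Step 2: put the difference where it can occur.** With d=0.5 in level 2 and zero in level 1, the averaged difference is 0.25 and f becomes 0.125.

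| Correlation of the two changes | λ, main effect | Power, main effect | Power, interaction |
|---|---|---|---|
| +0.50 (plan) | 0.015625·98·2/1.5 = 2.04 | 29% | 69% |
| 0 | 0.015625·98·2/1 = 3.06 | 41% | 41% |
| −0.50 | 0.015625·98·2/0.5 = 6.13 | 69% | 29% |

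A simulation with 20,000 runs at r=+0.50 gave 29.8% for the main effect and 68.8% for the interaction. For the main effect to reach 80% at N=98 and r=+0.50, the treatment-period difference must be about d=0.99.

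**Step 3: which correlation is plausible.** Suppose the three visits have equal variances and a common correlation ρ. Each change then has variance 2(1−ρ) and their covariance is −(1−ρ), so they correlate at −0.5 whatever ρ is. The two changes sum to T3−T1, so the main effect is a comparison of T3−T1 with variance 2(1−ρ) in raw-score units.

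**Step 4: compare the models on one footing.** Take d=0.5 in raw-score SD and 49 per arm, with λ = d²·(49/2)/V, where V is the variance of the contrast or residual.

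| Model | V | ρ=0.3 | ρ=0.5 | ρ=0.7 |
|---|---|---|---|---|
| Unadjusted main effect (T3−T1) | 2(1−ρ) | 54% | 69% | 89% |
| T3 adjusted for one earlier visit | 1−ρ² | 73% | 81% | 93% |
| T3 adjusted for T1 and T2 | 1−2ρ²/(1+ρ) | 75% | 85% | 96% |

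Worked case at ρ=0.5, last row: V = 1−0.5/1.5 = 0.667 and λ = 0.25·24.5/0.667 = 9.19, giving 85%.

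**Step 5: sensitivity to effect size.** With N=100, ρ=0.5 and both covariates, power is 23%, 44%, 68% and 86% for d=0.2, 0.3, 0.4 and 0.5.

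**The case against.** Four points can be made for the plan.

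- **The calculation contains no slip.** The 80% is what G*Power returns for the option chosen. This stands: the fault is a mismatch between option and design, not arithmetic.
- **The 29% rests on a correlation that the design makes unlikely.** This stands in part. A reader might infer that the planned ANOVA has 29% to 69% power, as one range. The documents do not support that, because the ends belong to different premises: 29% is the powered term at the plan's own r=+0.50, and 69% is the same term when the changes correlate at −0.5. The interaction reverses the two figures, but the protocol never names or powers it.
- **Symptom severity is to be considered as a covariate.** If that means the T1 outcome score, the main effect becomes T3 adjusted for T1, with about 73% to 93% power for ρ from 0.3 to 0.7. This is a reasonable reading and rules out a flat claim that the trial lacks power. But Study Design does not say which severity measure is meant, and neither of the sections that define and power the test contains that model.
- **The effect size is a judgement.** The protocol admits a lack of data and argues that daily feedback differs from earlier forms. A reader might infer that f=0.25 lies at the top of the published range. The Introduction says only that "Meta-analyses report small to medium overall effect sizes", without numbers, so its place in that range cannot be fixed from the document.

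It would also go too far to call the comparison biased: T3−T1 between randomised arms is a valid contrast. The issue is its power and how that power is described.

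**Conclusion.** The stated 80% does not describe the power to detect d=0.5 arising during treatment. At N=98 and alpha 0.05 (assumed), the term that was powered has 29% with the plan's own r=+0.50. With the correlation of about −0.5 that follows from equal variances and equal correlations across visits, it has 69%; in raw-score units that becomes 54% to 89% for ρ from 0.3 to 0.7.

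The 80% stands only if f=0.25 was meant as the difference averaged over both levels. At r=+0.50 that implies about d=1.0 during treatment, which is hard to reconcile with calling the value a lower threshold.

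The conclusion does not extend to saying that 100 patients are too few. An adjusted analysis of the visits already planned recovers most or all of the intended power at d=0.5. For smaller effects it does not. These figures assume complete data.

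**What to change.** - **Test.** Make the between-condition test the condition effect on T3 from an ANCOVA or mixed model adjusting for T2 and T1. Keep the waiting-period level for the separate question of treatment against waiting.
- **Consistency.** Align Study Design, Power Considerations and Statistical Analysis on that one model, and say which severity score is the covariate.
- **Power statement.** Replace the 80% with the power of that model at N=98 to 100. Show it over the assumed visit correlation and over d from 0.2 to 0.5, as in Steps 4 and 5.
- **Wording.** Drop or justify the description of f=0.25 as a lower threshold.

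The cost is rewording. T1, T2 and T3 are already collected, no patients are added, and the protocol reports 22 enrolled with no outcome analyses done, so the test can still be fixed without knowledge of results. The downside is that the stated power becomes conditional on an assumed correlation and is visibly low for small effects.

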## Results

Although the trial is ongoing, recruitment has already begun. As of the time of submission, 22 participants have been enrolled and have completed the diagnostic eligibility assessment. Data collection started in 2022 following the training of participating therapists in the use of the SNS, which was funded by the German Society for Autosystemic Hypnotherapy in 2022 and 2025. Data collection will continue until all follow-up assessments (T4) are completed, which is projected for the first quarter of 2027. No outcome analyses have been conducted to date. Study findings are expected to be disseminated in the second quarter of 2027.

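### The target of 100 leaves 2 patients above the 98 needed for the arm comparison, and the named ANOVA needs T3, so the stated 80% power is lost at about 4% loss

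*Protocol article*

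**What the plan says.** Power Considerations treats two questions. The wait-versus-treatment comparison needs 32 patients. For the arm comparison, "a lower threshold value of the mean effect size was supposed at f=0.25" and "The power was defined at 0.80"; the result is 98 patients, 49 per arm. The article then states that "we defined the overall sample size of this study as 100 patients", 50 per arm. It gives no dropout rate and no inflation, and it does not say that the 2 extra patients are meant for attrition. The Abstract counts the 100 as patients randomised after the waiting period.

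Under Statistical Analysis, "The statistical procedure for answering the outcome-related questions of this study is ANOVA with repeated measures", with condition as the between-subject factor and T1-T2 versus T2-T3 as the within-subject factor. Linear and multilevel regression models are mentioned as further options, with alliance and implementation quality among their predictors. How incomplete cases are handled is not stated.

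Study Design places T3 at the end of a treatment whose length patient and therapist agree case by case, and T4 six months later. Under Assessments, outcomes are completed in the app outside the sessions. In the Introduction, the article reports that earlier meta-analyses "showed that the feedback significantly reduces the odds of treatment dropout".

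**The concern.** A patient without T3 has no T2-T3 change and cannot enter the named ANOVA in its classical form. With an open-ended treatment before T3, zero loss is not a realistic planning assumption, yet the stated 80% allows for almost none. The sample size and its power are fixed in this article, so the shortfall is not a detail left to another document.

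There is also a risk to validity. Feedback is what randomisation varies, and the article's own background links feedback to lower treatment dropout. If more patients were lost from ASH alone, and those lost tended to do worse, the remaining ASH patients would look better than the whole arm. The feedback effect would then be understated.

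**Working it through.** **Inputs.** From Power Considerations: f = 0.25, correlation r = 0.50, m = 2 measurements, 2 groups, target power 0.80. Alpha is not stated; 0.05 is assumed, and it reproduces both of the plan's sample sizes. On the software, the article says: "The power calculation for estimating the sample size was realized by the software package G*Power".

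**Reproducing the plan's figures.** For the between-factor test, noncentrality is λ = f²·N·m / (1 + (m−1)·r), with 1 and N−2 degrees of freedom.

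- N = 98: λ = 0.0625 × 98 × 2 / 1.5 = 8.17, power 0.808.
- N = 96: λ = 0.0625 × 96 × 2 / 1.5 = 8.00, power 0.799.

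The smallest even N reaching 0.80 is therefore 98, as stated. For the within-subject question, λ = f²·N·m / (1−r) = 0.1156 × 32 × 2 / 0.5 = 14.8, which gives power 0.961 against the stated 96%.

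**Margin.** 100 − 98 = 2 patients, 1 per arm. With 97 analysed, power is 0.8035; with 96 it is 0.799. The target is missed from a loss of 4 patients in 100.

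**Power if 100 are randomised and only patients with T3 are analysed** (loss rates are assumptions):

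| Loss to T3 | Analysed | Power, arm comparison | Randomised to keep 98 (equal arms) |
|---|---|---|---|
| 0% | 100 | 0.816 | – |
| 5% | 95 | 0.795 | 104 |
| 10% | 90 | 0.773 | 110 |
| 15% | 85 | 0.749 | 116 |
| 20% | 80 | 0.722 | 124 |
| 30% | 70 | 0.663 | 140 |

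The last column is 49/(1 − loss) per arm, rounded up and doubled. All these figures refer to the test that the plan powered, the group main effect. The within-subject question keeps power above 0.99 even with 60 analysed.

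**Possible bias of a complete-case comparison.** None of these inputs is in the article. Let the outcome be standard normal and let the log odds of being lost rise by 0.5 or 1.0 per SD of worse outcome (odds ratios of about 1.6 and 2.7). The bias is the difference between the arms in how far the mean of the remaining patients shifts. It is compared with the planned effect, f = 0.25, which is d = 0.5.

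| Loss, ASH vs ASH+SPM | Bias against feedback | Share of d = 0.5 |
|---|---|---|
| 20% vs 15% | 0.024 to 0.041 SD | 5-8% |
| 20% vs 10% | 0.05 to 0.08 SD | about 10-16% |
| 30% vs 15% | 0.070 to 0.120 SD | 14-24% |

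**The case against.** The article does not say that only completers are analysed. It names repeated-measures ANOVA and is silent on incomplete cases; imputation before the ANOVA is possible, and missing-data rules commonly sit in an analysis plan that is not shown here. That stands. A reader might infer a completers-only analysis, but it follows from how the classical method works and is not stated. The optional multilevel models do not settle the matter, because alliance and implementation quality are measured after randomisation. A model that includes them is not an analysis of the randomised contrast.

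A reader might also infer that the authors expect less dropout under feedback in this trial. The documents do not support that. The sentence in the Introduction is background from earlier meta-analyses. For this trial the Abstract expects better symptom severity and engagement and does not mention dropout. Nor is stopping treatment the same as missing T3: the questionnaires are filled in outside the sessions, and nothing says that early stoppers are not assessed.

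The bias figures rest wholly on assumed rates, and their direction is against feedback, so they do not point to a false positive. They also assume dropout that depends on the outcome itself, a bias that a mixed model does not in general remove. Leaving T4 out of the arm comparison is a choice of endpoint, not an error.

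What the objection leaves untouched is the arithmetic: 98 required, 100 planned, no allowance, and a named analysis that needs T3.

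**Conclusion.** The point holds for the arm comparison. The stated 80% is correct for 98 analysed patients, but it is lost at about 4% loss after randomisation and becomes about 77% at 10% and 72% at 20%. This assumes alpha 0.05, the plan's own formula, the 100 counted at randomisation and analysis of patients with T3 only. If the 100 were counted at enrolment, losses during the waiting period would add to the shortfall. The wait-versus-treatment question is unaffected.

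Bias is a conditional risk. It needs a complete-case analysis together with losses that differ by arm and relate to outcome. Its size, about 0.02 to 0.12 SD, depends on the assumed rates.

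Accrual is a separate point. The Results section says "As of the time of submission, 22 participants have been enrolled and have completed the diagnostic eligibility assessment", with collection having begun in 2022, and also "Data collection will continue until all follow-up assessments (T4) are completed, which is projected for the first quarter of 2027". A reader might extrapolate a final sample size and its power from this. The article does not support that: it gives no submission date, and it reports a second round of training funding in 2025 that could change the pace. It does show that the target of 100 and the end date need to be reconciled.

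**What to change.** 1. Replace repeated-measures ANOVA as the main analysis of the arm comparison with a likelihood-based mixed model on all randomised patients, with T2 (and T1) as baseline and T3 as the outcome. Add a delta-adjusted sensitivity analysis, because the mixed model does not remove bias from dropout that depends on the unobserved outcome.
2. State that the T3 and T4 app questionnaires also go to patients who stop treatment early.
3. Restate power for the arm comparison as about 72-77% for 80-90 analysed patients.
4. Separately, reconcile the target of 100 with completion of T4 in the first quarter of 2027.

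The cost is revised analysis wording, one rule in the app and a less favourable stated power; no extra patients or staff are needed. The article reports that no outcome analyses have been done, so the change can still be made without knowledge of results.

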### Statistical Analysis

The statistical procedure for answering the outcome-related questions of this study is ANOVA with repeated measures, with the groups (conditions) as the between-subject factor and the comparison of the waiting period (T1-T2, level 1) with the overall treatment (T2-T3, level 2) as the within-subject factor. The preference ratings of the therapists in the ASH+SPM condition can be used as covariates in a 1-factor ANOVA with repeated measures.

The therapy effects can be predicted by linear regression models and multilevel regression models with conditions, therapy motivation (patients), alliance rates (patients), and the quality of the implementation as predictors. In the ASH+SPM condition, the preference of implementing the SPM (therapists) and the compliance rates (patients) of the process monitoring can also be used as predictors.

The research questions on the dynamics of change (eg, Are pattern transitions related to the outcome?) will be analyzed by applying the Pattern Transition Detection Algorithm [59] and methods of recurrence quantification analysis [60,61]. The respective quantifiers will be correlated with the outcome measures (T2-T3 and T2-T4).

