**Objective:**

This study aims to investigate the effectiveness of combining routine process monitoring with hypno-psychotherapy (autosystemic hypnotherapy) by comparing it to autosystemic hypnotherapy without process feedback in the outpatient treatment of mood disorders. It also seeks to examine process-outcome relationships and mechanisms of change through high-frequency self-assessments and session-based feedback.

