To obtain a deeper insight into the mechanisms of feedback procedures, it should be considered that there are different approaches to realize it. Depending on the paradigmatic frame of the procedure, which can be linear and standardized or nonlinear [10,11], there may be different mechanisms of intervening and creating effects. The linear approach usually focuses on standard tracks or expected treatment responses [12], based on infrequent measures (eg, session by session). The nonlinear frame is based on the conceptualization of psychotherapy as a self-organizing and chaotic process [10,11] and does not presume any assumptions on the shape of trajectories [13]. Presuming standard tracks, pathways of clinical change are expected to run on these tracks, with deviations being at risk of deteriorations or unfavorable developments [14,15]. In case of “not on track” courses, clinical support tools are offered [16]. Different from this, nonlinear monitoring and feedback is based on more frequent and equidistant measures (eg, daily assessments) and, in consequence, on continuous feedback interviewing and process reflection (eg, in every session or every second session). Sampling rates with frequent and equidistant measures allow for different options of analyzing the pathways (time series) of change [17]. No specific incidents (eg, “not on track” states) are required for executing feedback talks. A focus of interest is on occurring critical instabilities, which are valued as precursors of upcoming pattern transitions [18].

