Different from high-frequency process monitoring, the so-called routine outcome monitoring [19] focuses on outcome criteria, which are usually given by standard outcome questionnaires such as Outcome Questionnaire-45.2, Symptom Checklist-90-Revised, Depression Anxiety Stress Scales, or Beck Depression Inventory. The sampling rate is low, for example, each month or lower. In consequence, no real time series can be created. In contrast, the process monitoring approach as applied in this study includes a spectrum of common factors that have been proven to be important for creating successful treatments [20]. A Therapy Process Questionnaire (TPQ) was developed for daily self-assessments, which are not restricted to in-session evaluation but can be carried out in the real-world setting of the patients (eco-systemic approach). It includes factors as “well-being and positive emotions,” “emotional and problem intensity,” “motivation for change,” “insight/confidence/therapeutic progress,” and “mindfulness/self-care” [21].

Another difference exists between standardized and personalized procedures, with standardized approaches using predefined questionnaires, whereas personalized measures usually are based on case formulations as the idiographic system modeling and can be implemented by a questionnaire editor, as it is available in the synergetic navigation system (SNS) [22]. As practical experience shows, compliance rates can be optimized by personalized approaches of monitoring and feedback because they focus on patients’ own goals and topics [23]. The items of the questionnaires in use are created by the patients themselves, improving the experienced meaningfulness and thereby, the validity of the measures.

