### Aims of This Study

This study addresses different research questions. There is some concern regarding the implementation of the procedure into the routine practice of outpatient psychotherapists, which is challenging because of the complexity of the routine process monitoring procedure. It encompasses an assessment of the patient’s personal resources, a case formulation, and, based on this, the development of a personalized process questionnaire. Regular feedback interviews during the sessions are scheduled with reference to the visualized results. Other research questions focus on the outcome of this study’s conditions and on the patterns of change that may characterize successful or unsuccessful therapies. Potential therapists’ implementation effects will be examined based on an ABAB therapist allocation (see the Study Design section). The main research questions are as follows:

Practicability: Can high-frequency process monitoring (daily self-assessments) and feedback interviewing (at least every second session) be implemented in outpatient routine psychotherapy, that is, in naturalistic settings? To what extent is the routine practice of outpatient psychotherapy supported by process monitoring? What can be learned from this study for the implementation of process monitoring into practice and training?Treatment outcomes: What is the efficacy of ASH compared with a waiting period control? What are the differences in the treatment efficacy of the two randomized implementation conditions, ASH versus ASH supported by personalized process monitoring and feedback in self-reported primary and secondary outcomes?Session effects and change dynamics: What are the differences between the implemented conditions in the experienced quality of the sessions (eg, micro-outcome) and in the therapeutic alliance? Does the process feedback support the therapeutic alliance? With reference to the time series created by the daily self-assessments: Are there specific features of the change dynamics (eg, discontinuous pattern transitions and critical instabilities) related to the outcome?Therapist effects: Are there any differences across therapists (therapist effects)? Is there an interaction between potential therapists’ preferences for a particular implementation condition and outcome?

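### Quantifiers from daily series of patient-specific length are correlated directly with outcome change, so therapy length can create an association for length-dependent quantifiers, and the correlations describe co-occurrence, not mechanism

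*Protocol article*

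**What the plan says.** The third research question (Aims of This Study) is: "Are there specific features of the change dynamics (eg, discontinuous pattern transitions and critical instabilities) related to the outcome". The Statistical Analysis section says that this question "will be analyzed by applying the Pattern Transition Detection Algorithm [59] and methods of recurrence quantification analysis", and then: "The respective quantifiers will be correlated with the outcome measures (T2-T3 and T2-T4". No other step is given for it.

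Daily ratings exist only in the ASH+SPM arm, planned at 50 patients (Power Considerations; Strengths). They run during a treatment of no set duration. Under Study Design, "the treatment period starts, whose length depends on the concrete requirements of each patient", and patient and therapist decide on it together. T2 is the start of treatment, T3 its end, and T4 follows 6 months after the end.

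On the content of the daily standard questionnaire, the Introduction says: "It includes factors as “well-being and positive emotions,” “emotional and problem intensity", followed by motivation, insight and mindfulness factors. The Abstract states the purpose: "It also seeks to examine process-outcome relationships and mechanisms of change through high-frequency self-assessments and session-based feedback". Its Conclusions return to exploring change mechanisms.

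The only duration named as a possible covariate is waiting time, in the ANOVA (Limitations).

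**The concern.** There are two separate problems.

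**Length.** A longer series gives more opportunity for transitions to occur. Because patient and therapist set the length, it may depend on progress. If longer therapy goes with more improvement, or with less, a raw count of transitions will correlate with outcome even when the transition rate has nothing to do with outcome. The sign of the artefact follows the sign of the length-outcome relation, so slow responders kept longer in therapy would produce a negative correlation.

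**Overlap.** The daily items on well-being and problem intensity are rated between T2 and T3 by the same patients whose self-reported symptom change over T2-T3 is the outcome. Part of any association may be one change recorded twice. T2-T4 does not remove this, because it contains T2-T3.

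At stake is the interpretation of the process results. A significant correlation could be reported as evidence for a mechanism when it reflects time in therapy or shared content.

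**Working it through.** **The plan's own figures.** The article gives none for these correlations. Its ANOVA figures reproduce (power 0.808 at N=98 against the stated 80%; 0.961 at N=32 against 96%; two-sided 5% assumed) and play no part here. With 50 patients, a correlation needs |r| of at least 0.279 for p<0.05, and 80% power requires r of about 0.39.

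**Length: inputs.** Only n=50 comes from the article. Assumed: therapy length L is lognormal with mean 240 days and coefficient of variation (CV) 0.3-0.7; transitions are Poisson with mean L/60, at a rate unrelated to outcome; L correlates ρ with outcome.

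**Length: size of the spurious correlation.** The mean count is k = 240/60 = 4. The count has variance k + (CV·k)², and only the second term comes from length. So

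corr(count, outcome) = ρ · CV·k / √(k + (CV·k)²)

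- CV 0.3: 1.2/√(4 + 1.44) = 0.51, so 0.10, 0.15 and 0.26 for ρ = 0.2, 0.3 and 0.5.
- CV 0.5: 2/√(4 + 4) = 0.71, so 0.14, 0.21 and 0.35.
- CV 0.7: 2.8/√(4 + 7.84) = 0.81, so 0.16, 0.24 and 0.41.

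**Length: how often a nominal 5% test is significant** (simulation, n=50):

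| ρ | CV 0.5 | CV 0.3-0.7 |
|---|---|---|
| 0 | about 5% | about 5% |
| 0.2 | 16% | 10-22% |
| 0.3 | 32% | 19-40% |
| 0.5 | 68% | 44-79% |

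Dividing the count by L, or partialling out L, brings the rate back to about 4-6% throughout.

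**Overlap: quantifiers.** A second simulation gave every patient 200 days, so length played no part. Each series was an autocorrelated daily series (lag-one coefficient 0.5) plus a smooth linear gain proportional to the patient's own improvement, with no transitions. The assumed trend loading was 0.5-1.5.

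- Recurrence rate: mean correlation with outcome -0.17 to -0.54.
- Standard deviation of the series: 0.19 to 0.56.
- Both together: significant in 21-97% of samples, against 4-5% at zero loading.
- A local 14-day level-shift statistic: significant in only 6-11%.

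How far overlap matters therefore depends strongly on the quantifier.

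**Overlap: T2-T4.** T2-T4 change is T2-T3 change plus T3-T4 change. If the two parts are independent and the SD of T3-T4 is c times that of T2-T3, corr(T2-T3, T2-T4) = 1/√(1 + c²). This is 0.96 at c = 0.3 and 0.71 at c = 1.0. The longer window mostly repeats the shorter one.

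**The case against.** The strongest reply is that the research question asks only whether features of the dynamics are related to outcome, and a correlation answers that. This stands: the correlations are legitimate as description. They fall short only for the mechanism reading, which the Abstract invites.

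A second reply is that the article does not say which quantifiers enter. Recurrence measures that are proportions do not grow with exposure as a count does, and scaling may be settled in a fuller plan. This also stands as a limit. The length artefact applies to length-dependent quantifiers and disappears when length is unrelated to outcome. The point rests on the direct correlation that the article states, not on missing detail.

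Third, some mitigation is present. Compliance with monitoring may enter the regression models for ASH+SPM, and Strengths says session-level micro-outcomes and alliance can be aligned with the daily dynamics. Neither is attached to these correlations, and neither deals with therapy length.

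Two stronger readings are tempting. A reader might infer that the plan claims the dynamics precede the outcome and cannot show it, because instabilities are introduced as "critical instabilities, which are valued as precursors of upcoming pattern transitions". That sentence orders instabilities before transitions within the daily series and says nothing about T3. A reader might also infer that no outcome is measured after the process. T4 is measured 6 months after therapy ends; the fault is only that T2-T4 change includes T2-T3 change.

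**Conclusion.** The concern holds in limited form. As stated, the correlations can be produced by therapy length for length-dependent quantifiers, provided length is related to outcome. The false-positive rate is then about 10-22% for a weak relation (0.2) and 44-79% for a strong one (0.5), and stays near 5% if there is none. Mean length, its spread, the transition rate and the length-outcome correlation are all assumptions; the article gives no figure for any of them.

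Separately, the shared period and partly shared content mean that the T2-T3 and T2-T4 correlations show co-occurrence and cannot carry a conclusion about mechanisms. The overlap may be large for recurrence rate or series variability and small for a local level-shift measure. The documents do not support saying that daily change and symptom change are largely the same event: several daily factors are not symptom-like, and personalized items are added.

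This is a secondary question answered in one arm. The randomized comparison is unaffected.

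**What to change.** In the Statistical Analysis section:

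1. Express length-dependent quantifiers per unit time, or replace the simple correlation by partial correlation or regression with series length, completed rating days and T2 severity as covariates.
2. Add T3-T4 change as an outcome window. It lies wholly after the daily series, provided the ratings stop when treatment ends, which should be stated. It concerns maintenance after therapy, so it complements the planned windows.
3. Label the whole-series T2-T3 and T2-T4 correlations as descriptive. This applies after adjustment too, because length may itself depend on progress.

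Quantifiers from a fixed early window may be added as a sensitivity analysis. They should not replace the planned analysis: an early window drops later transitions, and outcomes are scheduled only at T1-T4, so no outcome score exists at its end.

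The cost is slightly more analysis work and a more modest conclusion; no new data are needed. Results reports that no outcome analyses have been conducted, so the wording can still be settled before results are seen.
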